### Core intervention

Brief verbal intervention for smoking cessation (BISC), which is a 1–3-minute verbal advice delivered by health professionals during routine consultations, is a highly effective and cost-efficient approach. Based on the China Clinical Smoking Cessation Guidelines, BISC includes: asking about smoking status, asking about the number of cigarettes smoked, discussing the harms and benefits of quitting, advising to quit, and providing a referral.

### Implementation strategies

*Optimization conceptual model*

An optimization conceptual model for the implementation of BISC was constructed, employing mixed methods guided by Diffusion of Innovation Theory. Based on this theory, attributes of an intervention strategy can facilitate intervention implementation, including compatibility, observability, trialability, relative advantage, and complexity. This conceptual model has integrated elements and their respective levels of implementation techniques and mechanisms that influence the implementation of BISC. We have developed a preliminary conceptual model based on our current understanding (Figure 3), which has undergone further refinement.

**Figure 3 F0003:**
[figure not shown]
Conceptual model for optimizing BISC implementation strategies within the MOST framework in primary healthcare, Guangdong, China

*Implementation strategy function*

The first phase of this study, which has been completed, was designed to systematically identify a set of implementation techniques for the optimization trial (Supplementary file Appendix A).

*Implementation strategy forms*

Following the identification of the strategy functions, the specific forms (i.e. the detailed actions and activities) for each strategy were developed and specified to ensure local relevance and feasibility. This process was guided by recommendations from the Proctor Implementation Strategy Reporting Specification^17^, and involved phased stakeholder interviews to validate and refine the checklist of strategies (Supplementary file Appendix B). The study subsequently involved stakeholders in identifying the specific forms (representing levels of implementation techniques), adhering to the principle of co-production. Discussions with stakeholders guided the selection of implementation techniques that were deemed consistent across all sites and those that were optional for testing in the factorial trial. The selection of constant components was based on ethical or logistical considerations, ensuring that specific intervention elements were uniformly delivered to all participants.

### Constant component

*Assessing readiness and identifying barriers and facilitators*

The strategy of assessing readiness and identifying barriers and facilitators will be included as a constant component across all eight experimental conditions. This ensures a baseline understanding of the implementation environment and addresses fundamental challenges uniformly across all participating sites.

A proactive assessment of the readiness of primary healthcare institutions and clinicians to implement BISC was conducted through an online questionnaire. This was completed within the first week of the project commencing. Conduct monthly online questionnaire and online focus group discussions to identifying contextual barriers and facilitators.

### Optional components

*Incentives*

This strategy aims to enhance BISC implementation through a multi-pronged incentive approach, primarily targeting clinicians and organizational commitment.

*Foundational training*

Within the first week of the project intervention commencing, third-party experts will conduct a one-time training for all medical staff, focusing on BISC skills. This pre-implementation incentive aims to enhance the hospital’s overall knowledge and skills regarding BISC.

*Issue an administrative directive*

Hospital administrators and middle-level leaders (e.g. department heads) will issue a unified administrative directive within 24 hours of foundational training, mandating clinicians to actively perform BISC. This action aims to ensure low time-cost for clinicians.

*Assessment and public disclosure*

The execution of BISC will be incorporated into medical service quality assessments. Weekly, in conjunction with medical quality surveys, the Medical Affairs Department or a third party will conduct random patient follow-up checks to assess BISC implementation, and public the results.

*Identifying and preparing champions*

This strategy focuses on establishing internal champions within the institutions to drive BISC implementation. The timeline for this strategy will be extended to ensure effective engagement and training.

*Identification*

Recruitment calls will be issued to all hospital staff, offering research funding as an incentive to attract promoters. This should be conducted within one week of the project commencing.

*Selection and empowerment*

Following identification , one-on-one motivational interviews will be conducted with interested candidates to help them understand the role. After selection, formal promoters will be appointed based on these interviews and administrative assessments. This combined approach provides a balanced method for selecting capable and motivated individuals.

*Cultivation*

This is initiated immediately after empowerment and continues throughout the entire project cycle. Identified promoters will receive BISC-related learning materials and begin participating in practical projects with the project team. This will involve monthly participation opportunities in communication and training processes, and the promoters will begin organizing small-scale internal trainings within their departments. This aims to deepen their understanding and improve overall implementation efficiency.

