## METHODS

### Study design

*Hybrid and full factorial design*

This study is designed as a type 3 hybrid implementation trial^14^, concentrating on the development and assessment of the effectiveness of a specific implementation strategy to enhance the adoption and implementation of BISC. The design prioritizes the evaluation of implementation strategies while also examining clinical outcomes. The research adheres to the principles of the Multiphase Optimization Strategy (MOST)^15,16^ with its core component being a 2×2×2 full factorial design (Figure 1). This design will result in eight distinct experimental conditions and allows for the evaluation of the main effects and potential interaction effects of the implementation techniques, which is the core purpose of the optimization trial. The study has identified four key implementation techniques to be included in the trial. One of these, assessing readiness and identifying barriers and facilitators, will be included as a constant component in all eight conditions, ensuring a foundational level of support for all participants. The remaining three techniques serve as the three factors of the factorial design, each with two levels (present or absent) (Table 1).

**Table 1 T0001:** Full factorial design (2×2×2) with constant components within a type 3 hybrid effectiveness-implementation trial of BISC in primary healthcare facilities with a sample of 640 clinicians, Guangdong, China, January 2026 – December 2026

*Experiment* *conditions*	*Constant component*	*Optional components to be tested*		
	*Assess for readiness and* *identify barriers and* *facilitators*	*Identify and prepare* *champions*	*Alter incentive/allowance* *structures*	*Conduct educational* *meetings*
1	Yes			
2	Yes	Yes		
3	Yes	Yes	Yes	
4	Yes	Yes		Yes
5	Yes		Yes	
6	Yes		Yes	Yes
7	Yes			Yes
8	Yes	Yes	Yes	Yes

Yes: means included in intervention. No: means not included in intervention. The specifics form (such as ‘ranking primary healthcare clinicians’ execution of BISC and providing spiritual rewards for excellence’) of each component (such as ‘Alter incentive/allowance structures’) will be developed by inviting stakeholders to work together, following the principles of co-production. BISC: brief intervention for smoking cessation.

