### Education and training

This strategy focuses on enhancing the knowledge and skills of all medical staff through structured educational activities. The frequency of these activities is designed to build momentum while avoiding an excessive burden on staff.

*Specialized workshops*

Starting from the first month, the project team will conduct periodic thematic workshops on BISC-related knowledge and lectures on execution for all hospital staff. These will be held monthly after the initial appointment of promoters. These will be held once a month.

*Embedded health education*

Starting from Week 1, it is imperative to reinforce the knowledge of tobacco control among healthcare professionals on a daily basis, utilizing a variety of concise formats to ensure effective dissemination of information.

*Training exchange*

Starting from Week 8, public health departments and department heads will organize periodic smallgroup salon activities and peer-sharing sessions for all hospital staff.

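### The incentive factor contains staff-wide BISC skills training, the same ingredient as the education factor, so its main effect cannot be credited to incentives; the education workshop schedule also refers to promoters who are absent in conditions 6 and 7

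*Protocol article*

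**What the plan says.** Under Study design, the protocol article makes champions, incentives and educational meetings the three two-level factors of a full factorial, and says the design "allows for the evaluation of the main effects and potential interaction effects of the implementation techniques". Table 1 sets out the eight conditions.

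Optional components describes the incentive factor as several elements. The first is foundational training: "third-party experts will conduct a one-time training for all medical staff, focusing on BISC skills". Its purpose is stated as follows: "This pre-implementation incentive aims to enhance the hospital’s overall knowledge and skills regarding BISC". A directive and weekly assessment with public disclosure follow. The champion factor includes a cultivation step in which "the promoters will begin organizing small-scale internal trainings within their departments".

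Education and training describes the third factor: "This strategy focuses on enhancing the knowledge and skills of all medical staff through structured educational activities". Its workshops are said to begin in the first month, but the next sentence reads "These will be held monthly after the initial appointment of promoters". Strategy coordination places the identification of promoters ahead of the thematic training.

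The closing paragraph of Data analysis says that main effects will show which techniques work, that interactions will be read as synergy or antagonism, and that both will feed the choice of the final strategy.

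**The concern.** The trial exists to decide which named technique to keep. That needs each factor's absent level to lack what defines the factor. Staff-wide instruction in BISC skills defines education, yet it is also delivered wherever incentives are assigned. A positive incentive effect could then come from the training, from the directive and disclosure, or from both. The education contrast becomes, in half of its comparison conditions, more training against some training. If the two trainings overlap in effect, the overlap will appear as antagonism between incentives and education. The decision step would take that as a property of the techniques.

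The workshop wording raises a second, smaller problem. If the schedule follows the appointment of promoters, it is undefined where education is assigned without champions.

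**Working it through.** **1. Conditions, from Table 1.** Champions (C): 2, 3, 4, 8. Incentives (I): 3, 5, 6, 8. Education (E): 4, 6, 7, 8.

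**2. Orthogonality.** With present = +1 and absent = −1, the I×E products are +1 in conditions 1, 2, 6, 8 and −1 in 3, 4, 5, 7, so they sum to 0. The same holds for C×I and C×E, and X′X is diagonal (8, 8, 8). The packages are not aliased.

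**3. Where staff-wide BISC training occurs (I or E).**
- Education present: 4 of 4 conditions. Education absent (1, 2, 3, 5): 2 of 4, namely 3 and 5.
- Incentives present: 4 of 4. Incentives absent (1, 2, 4, 7): 2 of 4, namely 4 and 7.

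On this ingredient the two factors have the same profile. Foundational training is never given without the rest of the incentive package, so no analysis of the data can separate the two.

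**4. Illustration of size.** Inputs from Sample size and power: baseline 33.9%; target 0.339 × 1.40 = 47.46%, which reproduces the stated figure; difference 13.56 points; design effect 2; 20% loss; 80 clinicians per condition.

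Assumptions (mine): education gives 13.56 points; foundational training gives a fraction f of that and adds nothing where education is present; the rest of the incentive package and champions do nothing. With f = 0.5:

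| | E absent | E present |
|---|---|---|
| I absent | 33.90 | 47.46 |
| I present | 33.90 + 6.78 = 40.68 | 47.46 |

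- Education effect: 47.46 − (33.90 + 40.68)/2 = 47.46 − 37.29 = 10.17 points.
- Incentive effect: (40.68 + 47.46)/2 − (33.90 + 47.46)/2 = 44.07 − 40.68 = 3.39 points, all of it training.
- Interaction (difference in differences): (47.46 − 40.68) − (47.46 − 33.90) = −6.78 points.

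Power = Φ{[d − 1.96·√(2p̄(1−p̄)/n)] / √[(p₁q₁ + p₂q₂)/n]}. Effective n per factor level is 4 × 80 / 2 = 160 without loss, and 320 × 0.8 / 2 = 128 with 20% loss. For f = 0.5 and n = 160: d = 0.1017, p̄ = 0.4238, so (0.1017 − 0.1083)/0.0550 = −0.12 and power is 0.45.

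| f | Education effect | Incentive effect | Interaction | Power for education, no loss | With 20% loss |
|---|---|---|---|---|---|
| 0 | 13.56 | 0 | 0 | 0.70 | 0.60 |
| 0.5 | 10.17 | 3.39 | −6.78 | 0.45 | 0.38 |
| 1 | 6.78 | 6.78 | −13.56 | 0.23 | 0.19 |

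If the trainings add up instead (f = 0.5, no redundancy), the I and E cell is 47.46 + 6.78 = 54.24. Education keeps 13.56 points and there is no interaction. The incentive effect is then (40.68 + 54.24)/2 − 40.68 = 6.78 points, again all training. Attribution therefore fails with or without redundancy; dilution and antagonism need redundancy.

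These powers take the design effect of 2 at face value and only show direction and rough size.

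**5. Workshop schedule.** Education is assigned in 4, 6, 7, 8. Promoters are appointed only under the champion factor, so they exist in 4 and 8 but not in 6 and 7. The first-month start can be applied in all four conditions; the promoter-based start only in two. If the teams follow the second wording, workshop timing could differ by champion level.

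**The case against.** The strongest defence is that a factor may be a bundle. The incentive strategy is openly multi-pronged, its content was co-produced with stakeholders, and the packages are orthogonal. If the package works, it would be adopted with its training included. This stands: a reader might infer that the main effects are confounded and cannot be estimated, and the design does not support that. It does not rescue attribution, because the stated purpose is to choose between techniques, and one bundle contains the ingredient that defines another.

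Four further inferences go beyond the text:
- A reader might conclude that the workshops cannot run in conditions 6 and 7. The project team delivers them, one sentence starts them in the first month, and the education section ties neither the daily education nor the exchange sessions to promoters. The problem is a contradiction about timing.
- A reader might count promoter-run sessions as equal to expert training and say that only condition 1 is free of training. These sessions are small-scale and an ordinary champion activity. They belong in the description of the champion package and are not on the same footing.
- A reader might call an antagonistic interaction built in. It arises only if the trainings overlap in effect, which the article does not say.
- A reader might see a conflict between the incentive text and the ranking-and-reward example under Table 1. That note offers only an example.

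It is also fair to say that changing content may be late. The study period begins in January 2026, the article is dated March 2026, and the readiness assessment is reported in the past tense, although the Conclusions call the trial forthcoming.

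**Conclusion.** The point holds as one of attribution and interpretation. Package-level effects are defined and orthogonal. The incentive effect cannot be assigned to incentives as distinct from training, because staff-wide BISC training is present in every incentive condition and in two of the four education-absent conditions. This follows from the text and Table 1 without any numerical assumption.

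The amount of dilution is not known from the article. Under the f = 0.5 redundancy scenario the education effect drops by about a quarter, from 13.56 to 10.17 points, with the loss of power shown above. Under additivity it does not drop at all. That undiluted power is itself below 0.80 is a separate matter.

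The workshop start is stated in two incompatible ways for conditions 6 and 7 and needs to be reconciled.

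**What to change.** 1. Put the foundational training in one place only. In the education factor it would still run in four conditions, so no sessions are added. In the constant component it would run in all eight, which adds sessions in four. Either way, co-produced package content changes, which is a small but real cost.
2. If delivery has begun, leave the content alone. Define and report the incentive effect as that of a package including a one-time training, and the champion effect as that of a package including small-scale promoter-run training. State that neither will be attributed to the named technique alone, and carry this into the decision step, including how an incentive-by-education interaction is read. This costs wording only.
3. Reconcile Education and training and Strategy coordination with Table 1, so that one workshop schedule applies in conditions 4, 6, 7 and 8 and does not depend on promoters. This is also wording only.

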### Education and training

This strategy focuses on enhancing the knowledge and skills of all medical staff through structured educational activities. The frequency of these activities is designed to build momentum while avoiding an excessive burden on staff.

*Specialized workshops*

Starting from the first month, the project team will conduct periodic thematic workshops on BISC-related knowledge and lectures on execution for all hospital staff. These will be held monthly after the initial appointment of promoters. These will be held once a month.

*Embedded health education*

Starting from Week 1, it is imperative to reinforce the knowledge of tobacco control among healthcare professionals on a daily basis, utilizing a variety of concise formats to ensure effective dissemination of information.

*Training exchange*

Starting from Week 8, public health departments and department heads will organize periodic smallgroup salon activities and peer-sharing sessions for all hospital staff.

### Strategy coordination

The phased timeline for these strategies is designed to be realistic and manageable for clinicians in a busy primary care setting. The activities are staggered, with promoter identification taking place first, followed by a more gradual rollout of thematic training and exchange sessions to avoid overwhelming staff and to facilitate effective skill building over time.

### Ethical considerations

The study has been approved by the Biomedical Ethics Committee of Southern Medical University. A waiver of informed consent for obtaining service owner or clinician participation has also been granted. This waiver is crucial to mitigate potential observation bias, such as the Hawthorne effect^18^, as the use of USPs requires that clinicians are unaware they are being evaluated.

The institutional review board will oversee the study, ensuring that the rights of human subjects are protected. A Data and Safety Monitoring Board (DSMB) will be used to provide independent supervision. While minimal risks are associated with this study, any adverse events will be reported to the appropriate investigators and institutional review board as per standard procedures. Furthermore, all research staff will be trained on the importance of privacy. To protect participant confidentiality, a unique research ID will be assigned to each participant, and all data will be stored in password-protected electronic files or locked cabinets. Data extracted from medical records will not be linked to patient-identifying data. Moreover, all audio recordings will be erased at the end of the project.

### Study variables

*Demographic variables*

Demographic variables include institution information, clinician sociodemographics, and patient sociodemographics. Detailed variables, data collection methods, and time points are summarized in Table 2.

**Table 2 T0002:** Study variables of the type 3 hybrid effectiveness-implementation trial, Guangdong, China, January 2026 – December 2026

*Category*	*Outcome* *type*	*Variable*	*Theoretical basis*	*Definition*	*Variable type*	*Tool*	*Acquisition* *methods*	*Study periods ^a^*				
								*I*	*II*	*III*	*IV*	*V*
**Basic information**	Institution information	Institution location, level, etc.		-	-	-	Questionnaire survey	●				
	Socio-demographic of clinician	Gender, age, title, department, etc.		-	-	-	Questionnaire survey	●				
	Socio-demographic of patient	Gender, age, primary diagnosis, etc.					Telephone callback		●	●	●	●
**Implementation outcomes**	Primary outcome	Clinician asks smoking status	IOF: Fidelity RE-AIM: Implementation	From the first step in the BISC implementation steps in the China Clinical Cessation Guidelines (2015 edition), indicating whether the clinician asked smoking status or not.	Quantitative data, dichotomous variable (0,1)	Questionnaire	USP visit/telephone callback^b^		●	●	●	●
		Clinician advises to quit	IOF: Fidelity RE-AIM: Implementation	From the fourth step in the BISC implementation steps in the China Clinical Cessation Guidelines (2015 edition), indicating whether the clinician advised to quit.	Quantitative data, dichotomous variable (0,1)	Questionnaire	USP visit/telephone callback^b^		●	●	●	●
	Secondary outcome	Clinician asks about number of cigarettes smoked	IOF: Fidelity RE-AIM: Implementation	From the second step in the BISC implementation steps in the China Clinical Cessation Guidelines (2015 edition), indicating whether the clinician asked about number of cigarettes smoked.	Quantitative data, dichotomous variable (0,1)	Questionnaire	USP visit/telephone callback		●	●	●	●
		Clinician discusses the harms and benefits of quitting	IOF: Fidelity RE-AIM: Implementation	From the third step in the BISC implementation steps in the China Clinical Cessation Guidelines (2015 edition), indicating whether the clinician told about harms/benefits of quitting.	Quantitative data, dichotomous variable (0,1)	Questionnaire	USP visit/telephone callback^b^		●	●	●	●
		Clinician provides a referral	IOF: Fidelity RE-AIM: Implementation	From the fifth step in the BISC implementation steps in the China Clinical Cessation Guidelines (2015 edition), indicating whether the clinician referral patient to smoking cessation clinic.	Quantitative data, dichotomous variable (0,1)	Questionnaire	USP visit/telephone callback^b^		●	●	●	●
		Coverage of BISC delivery	IOF: Penetration RE-AIM: Reach	Percentage of patients who received BISC as compared to the patients who attended to PHC.	Quantitative data, percent (0–100%)	Questionnaire	USP visit/telephone callback^b^		●	●	●	●
	Tertiary outcome	Applicability of BISC delivery	IOF: Feasibility	The extent to BISC can be successfully carried out within PHC clinician.	Quantitative data 0–100 points	NPT questionnaire	Questionnaire survey				●	
		Acceptance of BISC delivery	IOF: Acceptability REAIM: Adoption, Maintenance	The perception among the PHC facilities that BISC implementation techniques is agreeable, palatable, or satisfactory.	Qualitative data	Interview outline	Semi-structured interview				●	
			IOF: Adoption RE-AIM: Adoption	The intention, initial decision, or action to try or employ BISC from the perspective of the PHC facilities.							●	
			IOF: Appropriateness RE-AIM: Adoption	The perceived fit, relevance, or compatibility of BISC for the PHC facilities; and/or perceived fit of BISC to address a particular issue or problem.							●	
		Sustainability of BISC delivery	IOF: Sustainability RE-AIM: Adoption, Maintenance	The possibility to BISC is maintained or institutionalized within PHC clinician’s ongoing, stable operations.	Quantitative data	The Program Sustainability Assessment Tool (PSAT)	Questionnaire survey				●	
		Sustainment of BISC delivery	IOF: Sustainability; RE-AIM: Maintenance	The continued implementation of BISC by the primary care clinician over time.	Quantitative data and qualitative data	The Provider Report of Sustainment Scale (PRESS) and interview outline	Questionnaire survey and semi-structured interview					●
		Cost of BISC delivery	IOF: Implementation Cost RE-AIM: Implementation	The cost of implementation, depends upon the costs of the BISC implementation techniques.	-	Administrative data					●	
**Effectiveness outcomes**	Secondary outcome	7-day point abstinence status		Self-reported abstinence from smoking for the past 7 days.	Quantitative data and qualitative data	-	Telephone callback			●	●	●
		Daily cigarette consumption		Number of cigarettes smoked daily. To assess a reduction in smoking behavior.	Quantitative data and qualitative data	-	Telephone callback			●	●	●
	Tertiary outcome	Patient satisfaction with the BISC provided by the clinician		The patient’s perceived satisfaction with how the physician implemented BISC during the consultation.	Quantitative data and qualitative data	-	Telephone callback			●	●	

a I: Enrolment. II: Baseline (i.e. before the first of BISC implementation). III: Mid-term (i.e. at the middle of BISC implementation), which will be executed the weeks 1, 3, 5, 7, 9 and 11 after the start of the BISC implementation. IV: Endline (i.e. at the end of BISC implementation). V: Follow-up (i.e. maintenance of the BISC), which will be executed 6 months after the endline.

b Data collection via telephone callbacks with patients in periods I and V; Data collection by USP visits in period IV. IOF: Implementation Outcomes Framework. BISC: brief intervention for smoking cessation. USP: unannounced standardized patient.

*Outcomes*

The study outcomes will be aligned with the principles of Proctor’s Implementation Outcomes Framework (IOF) and the RE-AIM framework. According to the type 3 hybrid design, the outcomes are categorized into primary and secondary aims to reflect the dual focus on implementation strategies and patient-level effects.

Primary aim: implementation outcomes

The primary aim of this study is to evaluate the effectiveness of the implementation strategies. These outcomes will be assessed by a combination of methods to ensure a comprehensive evaluation.

The primary outcomes, ‘clinician ask smoking status’ and ‘clinician advise to quit’, will be assessed using unannounced standardized patient (USP) visits. These outcomes serve as key measures of fidelity to the brief intervention protocol. The secondary outcomes, ‘clinician ask about number of cigarettes smoked’, ‘clinician discuss the harms and benefits of quitting’, and ‘clinician provide a referral’, will also be measured using a combination of USP visits for clinicians and telephone callbacks for outpatients.

The use of USPs is intended to mitigate observation bias and provide a valid, objective, and precise measurement^18,19^. We will employ three USP cases involving male current smokers with hypertension, type 2 diabetes, and cold, all requiring clinicians to provide BISC per national clinical practice guideline (Supplementary file Appendix C). Previously, our study developed, validated, and implemented 11 USP cases^20^ to evaluate the quality of PHC services, which contain a quality assessment checklist for the correct disposition of the physician in the desk design (Supplementary file Appendix D). These cases are reflective of the most prevalent conditions encountered in the PHC provider. The present study employed a standardized and well-established USP recruitment, training, and quality-control system based on the research team’s prior USP-based projects. Based on our previous experience, where a single USP can complete up to 72 visits per month, recruiting 20 USPs is sufficient to cover all 640 clinicians. In total, 20 USPs will be recruited across three regions, with approximately 6–7 USPs allocated to each city. All clinicians in the PSUs (a total of 640) will receive at least one USP visit. Each USP is scheduled to conduct a total of 32 visits. USP assignments to clinicians and clusters are performed using a random number table to ensure randomization and balanced coverage across clusters.

The sustainability of BISC delivery, defined as the likelihood of the intervention being maintained in practice, will be measured using the Program Sustainability Assessment Tool (PSAT)^21^. The sustainment of BISC delivery, or continued implementation over time, will be measured six months after the intervention. As USP visits are not suitable for long-term follow-up due to the risk of the standardized patients being recognized by clinicians, we will measure sustainment using the Provider Report of Sustainment Scale (PRESS)^22^ and semi-structured interviews to assess clinicians’ self-reported behavior and perceptions. The appropriateness of BISC delivery will be measured by Normalization Process Theory (NPT)-guided questionnaires (Supplementary file Appendix E)^23^, while its acceptability will be assessed through semi-structured interviews. Lastly, costs associated with the implementation strategies will be measured using administrative data.

Secondary aim: effectiveness outcomes

The secondary aim of this study is to assess the effects of the BISC intervention on patient-level outcomes. These outcomes will be measured via a patient phone call survey at two distinct time points. At the end of the intervention, a phone call will be made to all patients who were identified as smokers and received the BISC intervention during the study period. This initial survey will assess their smoking status immediately following the intervention and confirm their receipt of the BISC components. A 6-month follow-up survey will then be conducted exclusively with patients who self-reported as smokers and received the BISC intervention. This survey will assess the long-term effectiveness of the intervention by measuring key indicators, including 7-day point abstinence status, daily cigarette consumption, and patient satisfaction with the BISC provided by the clinician. A summary of all outcome measures, their respective assessment methods, and time points is presented in Table 2.

